# Testing the Mechanism of Action of Computerized Cognitive Training in Young Adults with Depression: Protocol for a Blinded, Randomized, Controlled Treatment Trial

**DOI:** 10.20900/jpbs.20200014

**Published:** 2020-06-19

**Keywords:** computerized cognitive training, depression, magnetic resonance imaging, clinical trials

## Abstract

**Background::**

Depression is associated with a broad range of cognitive deficits, including processing speed (PS) and executive functioning (EF). Cognitive symptoms commonly persist with the resolution of affective symptoms and increase risk of relapse and recurrence. The cognitive control network is comprised of brain areas implicated in EF and mood regulatory functions. Prior research has demonstrated the effectiveness of computerized cognitive training (CCT) focused on PS and EF in mitigating both cognitive and affective symptoms of depression.

**Methods::**

Ninety participants aged 18–29 with a current diagnosis of major depressive disorder or persistent depressive disorder, or a Hamilton Depression Rating Scale score ≥12, will be randomized to either PS/EF CCT, verbal CCT, or waitlist control. Participants in the active groups will complete 15 min of training 5 days/week for 8 weeks. Clinical and neuropsychological assessments will be completed at baseline, week 4, week 8, and 3-month follow-up. Structural and functional magnetic resonance imaging (fMRI) will be completed at baseline and week 8. We will compare changes in mood, cognition, daily functioning, and fMRI data. We will explore cognitive control network functioning using resting-state and task-based fMRI.

**Results::**

Recruitment began in October 2019; we expect to finish recruitment by April 2022 and subsequently begin data analysis.

**Conclusions::**

This study is innovative in that it will include both active and waitlist control conditions and will explore changes in neural activation. Identifying the neural networks associated with improvements following CCT will allow for the development of more precise and effective interventions.

**Trial Registration::**

ClinicalTrials.gov
NCT03869463; https://clinicaltrials.gov/ct2/show/NCT03869463.

## INTRODUCTION

Depression is a widespread public health issue with 20.2% of adults aged 18–29 reporting at least one episode of depression over the course of their lifetime, and 12.9% reporting at least one depressive episode in the past 12 months [1]. Depression is associated with affective symptoms as well as a range of impairments in social [2], occupational [3–5], and educational functioning [2], physical difficulties [6–8], and suicide [9]. Emerging adulthood (ages 18–29) represents a distinct transitional period in development with unique changes such as decreased family contact, the introduction of new significant friendships and romantic relationships, and increased financial responsibility [10]. Furthermore, the prevalence of depression and other psychiatric disorders is significantly higher in emerging adults than in any other age group [11]. Taken together, young adults aged 18–29 with depression represent an important, distinct population to target for novel treatment options.

The most common treatment for depression is antidepressant medication; however, only 60% of individuals achieve remission with their first treatment [12]. Additionally, depression falls on a continuum, and individuals with minor depressive symptoms who do not meet diagnostic criteria for major depressive disorder (MDD) still experience similar deficits in daily functioning [13–17]. Individuals who fall below the threshold of MDD diagnosis or who do not respond to antidepressants require novel interventions to address the associated impairments.

Depression is associated with a broad range of cognitive deficits in multiple domains including attention, verbal memory, processing speed, and executive functioning [18]. These cognitive deficits significantly affect the quality of life of those with depression and interfere with treatment of mood symptoms [19–22]. The existence and severity of the cognitive deficits are the strongest predictors of functional and treatment outcomes in depression [23–26]. The two most commonly and deleteriously impacted cognitive areas in depression are processing speed (PS) [19,27–29] and executive functioning (EF) [30–34]. Indeed, emerging adults with depression score significantly worse on tests of EF and PS than controls [32]. Processing speed is a lower-level, or fundamental cognitive resource, that facilitates the operations of higher-level (including executive) functions [35]. Existing treatments, such as antidepressants and psychotherapy, do not directly target these cognitive processes. This is important because targeting cognition may enable individuals to better benefit from interventions that target affective symptoms [19].

Computerized cognitive training (CCT) is an intervention that directly targets cognitive functions as a means to mitigate both the affective and cognitive symptoms associated with depression. CCT is comprised of exercises that strengthen specific cognitive processes via repeated practice [36]. Evidence of the effectiveness of CCT in improving cognitive functioning has been found in populations ranging from healthy adult populations [37,38] to diagnostic conditions including ADHD [39–41], schizophrenia [42], bipolar disorder [43], traumatic brain injury [44,45], minor neurocognitive disorder [46], and Alzheimer’s disease [47]. Beyond CCT’s effect on cognitive functioning, previous research has identified areas of improvement in other symptom domains following a course of CCT. Particularly, in a meta-analysis of CCT in depression, significant improvements were found in cognitive areas such as attention and working memory, as well as in affective symptomatology and everyday functioning, areas not directly targeted by CCT [48].

CCT specifically targeting processing speed (PS) may have particular benefits. In the Advanced Cognitive Training for Independent and Vital Elderly (ACTIVE) study focusing on older adults, PS-focused CCT was associated with significant reduction of 5-year mortality rates [49], risk of quality of life decline after 5 years [50], and greater likelihood of improvement in sense of personal control over one’s life after 5 years [51] when compared to other types of CCT. PS-focused training was also associated with reduced risk for depression after 1 year [49]. Similar findings have been reported in younger adults as well [52–57].

PS is of particular importance because decreased PS might prevent higher order mental operations from being executed properly. In depressed populations, previous research has found that PS mediates performance on tasks of executive function [28,58]. Given the relevance of PS in depressed populations, we propose a model of cognitive influence on mood regulation that places processing speed at the center, mediating the relationship between executive dysfunction and mood dysregulation [59]. With deficits in PS, information is processed too slowly, leading to the inability to perform executive functions. Failure to perform executive functions, such as inhibition, problem solving, planning, and flexibility, makes it difficult to regulate mood, which leads to increased rumination, worry, inability to suppress thoughts, and inability to select and modify adverse situations and behaviors.

In a preliminary study, we tested how different types of CCT may show different results [60]. When comparing PS/EF CCT to verbal-based CCT in young adults with depressive symptoms, the PS/EF group had greater gains in executive functioning and processing speed than the verbal group. Additionally, both groups saw significant and comparable improvements in self and clinician-rated depression severity and everyday functioning, though the PS/EF group obtained equivalent improvement in half the training time. Consistent with our model, PS/EF-targeted CCT may be more efficient than verbal ability-targeted CCT.

To elucidate the mechanism of action of CCT on mood, cognition, and everyday function, our proposed study will expand on the preliminary study by exploring the neural mechanism of action that underlies these improvements. Subserving EF and mood regulatory functions is the cognitive control network (CCN), an externally-oriented brain network comprised of two subnetworks, the frontoparietal network (FPN) and cingulo-opercular network (CON), and subcortical structures, including the thalamus and basal ganglia [61–63]. The FPN is composed of the frontal eye field, supplementary eye field, mid frontal gyrus, intraparietal sulcus, and superior parietal lobule [61,64]. The CON consists of the anterior cingulate cortex (ACC) and anterior insular cortex [65,66]. The CCN is ordinarily activated when engaged in a purposeful, goal-oriented task. Additionally, the CCN is involved in error detection and resolution [67], emotional processing [68], and information processing [69]. In young adults with depression, however, the CCN fails to come online when performing an executive task [70], and conversely, has greater functional connectivity at rest, indicating a failure of deactivation in the absence of cognitive effort [71]. Subthreshold depression has also been associated with impaired resting-state functional connectivity of the CCN [72]. This results in difficulties with attention, inhibitory control, novel generativity, planning, and working memory in individuals with depression [73,74]. Furthermore, fMRI studies using an emotionally-valenced go/no go task of behavioral inhibition and set shifting have shown different activation patterns in depressed patients as compared to healthy controls in areas such as the lateral orbitofrontal cortex, rostral ACC, and anterior medial prefrontal cortex [75], indicating an overlap with the CCN.

Given that non-specific cognitive training has been found to increase cortical thickness in the prefrontal cortex (PFC) [45], one distinct possibility is that CCT restores this neural network.

The CCN has purposes beyond cognitive processes alone. The CCN is connected structurally and functionally to other limbic areas (such as the amygdala, hippocampus, and dentate gyrus) acting as a regulator of affective states. Disruption in this cortico-limbic connection is thought to be central to mood dysregulation in young adults with depression [76]. Further, the magnitude of increased functional connectivity within the CCN when at rest significantly predicts the severity of depressive symptoms [70,77]. The CCN is also related to antidepressant treatment response. Poor antidepressant treatment response is associated with impaired functional connectivity of the CCN as well as damage to the ACC and dorsolateral prefrontal cortex (DLPFC) [78], whereas successful antidepressant treatment appears to alleviate deficits in the CCN [68]. Thus, the relationship between lack of response to antidepressant treatment and executive dysfunction is likely mediated by CCN integrity. PS/EF training may result in greater and more efficient improvement by directly targeting the CCN, with improvements in cognitive control and emotional processing corresponding to restorations of the dysfunctional network in depression. As such, there may be a greater increase in CCN activation and connectivity after CCT as compared to waitlist control, with a greater effect seen for PS/EF CCT than verbal CCT (active control).

Additionally, this study aims to address a major limitation of prior CCT research. While most CCT trials included a waitlist control condition, this study will include both active and waitlist control conditions. The active control condition will allow us to control for statistical regression to the mean, systematic selection biases, and non-specific effects of expectancy, engagement, motivation, and novelty associated with any type of engagement with cognitive training [79,80]. With the inclusion of the active control and waitlist control conditions, we will be able to isolate the effects of the PS/EF CCT and identify the neural mechanism of action that is specific to this type of training.

Thus, the primary aim of this study is to determine whether PS/EF CCT is superior to, and leads to faster improvement than, verbal ability CCT and waitlist control. The secondary aim of this study is to determine whether PS/EF CCT leads to greater change in CCN activation and connectivity than verbal ability CCT and waitlist control.

## METHODS

### Study Design Features and Rationale

Ninety young adults exhibiting mild to moderate depressive symptoms will be randomized in an 8-week computerized cognitive training (CCT) trial delivered via smartphone application. Mobile-based CCT was chosen as it is particularly relevant for young adults, with 92% of those aged 1829 owning a smartphone [81]. Mobile CCT is also consistent with the goal of personalizing medicine as it is easily accessible, inexpensive, noninvasive, and scaled to the skill level of each individual. Neuropsychological and clinical assessments will take place at Queens College, City University of New York, and fMRI will be conducted at The Graduate Center’s MRI facility, the Advanced Science Research Center. Participants will be randomized to one of three conditions: processing speed/executive functioning (PS/EF) CCT, verbal ability CCT (active control), or waitlist control (undergo assessment and imaging procedures and will be not be given access to the training program until 8-week completion). The randomization sequences will be balanced in blocks of random size to prevent researchers from guessing what the next participant’s condition assignment might be. In order to reduce expectancy bias, the informed consent signed by all participants prior to participation will not indicate which condition is the intervention, the active control, or the waitlist control. Instead, the consent will indicate that the participant will be assigned to one of three groups, two which target different aspects of brain functioning and the third which will begin cognitive training after 8 weeks.

### Role of Sponsor

The study is funded by a National Institute of Mental Health (NIMH) grant and internally supervised by a Data Safety Monitoring Plan. We customized a specific set of CCT training modules for participants in the PS/EF CCT condition and the verbal CCT condition using the mobile phone platform and application for cognitive brain training, Peak. These modules were also used in our preliminary study [60]. Over the course of this study, the Peak training modules will remain consistent for all participants. The current version of Peak is version 5.9; any updates that Peak makes to the application will not affect the specific games available to the research participants. Participants will access Peak on their mobile phones after they are provided with account information. Peak provides the research platform for free and does not have a role in the final study design, data interpretation, or publication of results. Participants will not be required to pay for the Peak account and will not have any post-study commitments to continuing to use Peak. None of the study team have any financial conflicts with Peak.

### Recruitment and Eligibility

Young adults with subthreshold depression, persistent depressive disorder, and mild to moderate major depressive disorder will be recruited from flyers posted in the community and local clinics, from self-referrals after participating in other studies for course credit at Queens College, and from an open-access website (i.e., Craigslist).

#### Inclusion/exclusion criteria

Detailed inclusion/exclusion criteria are described in Table 1. Notable inclusion criteria include a restricted, inclusive age range of 18–29; current diagnosis of major depressive disorder/persistent depressive disorder or an HDRS score ≥ 12; IQ score ≥ 85; daily access to a smartphone or tablet with internet connection; and willing and able to complete fMRI, mood, and neuropsychological testing. Intellectual functioning will be estimated using the Wechsler Test of Adult Reading (WTAR). The cutoff score of 85 was used to include individuals with IQ > 16th percentile in order to ensure that individuals have capacity to consent. This cutoff was also used in our preliminary study [60].

Participants will be excluded from participation if they lack English-speaking ability; have evidence of a major psychiatric, neurological, or medical disorder; severe depression (HDRS ≥ 30); active suicidal ideation, intent, plan, or have attempted suicide within the past year; use of medications that negatively impact cognition; history of drug or alcohol abuse or dependence within the past year; or regularly take part in online brain training (≥2 times per week). Participants will not be excluded for simultaneous engagement in psychotherapy or pharmacotherapy, or for use of medications that could be considered “cognitive enhancers” (e.g., Ritalin), as CCT may be considered a supplemental treatment that can be used in conjunction with evidence-based treatments for depression, until CCT has been established as a primary treatment. Furthermore, a recent meta-analysis of CCT in depression revealed that concurrent treatments did not affect the significant findings of small-moderate improvements in symptom severity and daily functioning and moderate-large effects on measures of EF [48]. However, once enrolled in the study, participants will be asked to refrain from beginning therapy or new medications, if possible, for the duration of the acute 8-week trial.

#### Depressive symptoms criteria

Depressive symptoms will be assessed at screening and all subsequent visits by the Hamilton Depression Rating Scale (HDRS). The central aim of this study is to demonstrate the mechanism of action of CCT, so in order to be as inclusive as possible of the depressive spectrum, inclusion criterion will be an HDRS score ≥ 12. Literature identifies mild forms of MDD as HDRS scores ranging from 8 to 16 [82]. Severe MDD (HDRS ≥ 30) will be excluded in order to ensure such individuals receive appropriate evidence-based treatment. The Beck Depression Inventory, Second Edition (BDI-II) will be used as a secondary measure of depressive symptoms. This self-report scale will be administered at all in-person visits and through an online survey format in weeks 2 and 6. The online administration of the BDI-II has similar psychometric properties as the in-person administration [83]. The HDRS and BDI-II were chosen over other depression rating scales to ensure compatibility of study results with other studies and to have both subject-rated and clinician-rated measures.

### Length of Clinical Trial

The length of this clinical trial will be 8 weeks. There is currently no consensus on the minimum amount of time spent in CCT required for therapeutic benefit, with training times ranging from 90 min [3,84] to over 1000 minutes [85] across successful programs for adults with depression. The choice of 8 weeks is also based on the success of an 8-week pilot study. In both the pilot study and the current study, the training protocol is 15 min per day × 5 days × 8 weeks, which equals 600 total minutes of training time. This amount appears to be more than sufficient in providing therapeutic benefit [60]. A follow-up visit will be conducted 3 months after the trial ends to determine lasting effects of CCT on mood, cognition, and daily functioning. Thus, the total study duration will be 20 weeks of participation. Since this study is considered low risk, harm from participating in this trial is not anticipated.

### Treatment Regimen

An initial pre-screening will be completed over the phone to assess initial eligibility criteria. Participants will provide information regarding age, access to smartphone/tablet, MRI contraindications, current/prior engagement in brain training games, and a brief medical history. If deemed eligible, participants will be invited for an in-person eligibility screen, which will assess for depressive symptoms and risk. Participants will be enrolled into the study after screening for eligibility and providing in-person informed consent. The randomization will be assigned by the statistician and then carried out by the unblinded research coordinator. Enrolled participants will engage in four clinic visits (weeks 0, 4, and 8, and 3-month follow-up) and receive two fMRIs (weeks 0 and 8). Participants will also complete an online version of the BDI-II during weeks 2 and 6. To protect study participants, if a participant shows a 20% increase from their baseline BDI-II score for two consecutive timepoints they will be discontinued from the study and provided with referrals for mental health services. This cut-off was made as a clinical decision based on data from our preliminary study [60] as well as research that shows that the minimal clinically important difference for improvement on the BDI-II is a 17.5% reduction in scores [86]. If a 17.5% reduction in BDI-II scores corresponds to a clinically important improvement, it is likely that a similar increase in scores would be a clinically important exacerbation. In our preliminary study [60], the mean baseline score on the BDI-II was 22.98 (SD = 11.58), so a 20% increase would be analogous to a shift from a score of 23 to a score of 28 for two consecutive timepoints. Additionally, BDI-II scores in general, as well as specific items, will be closely monitored. In particular, item 9 of the BDI-II, which assesses for suicidality, will be monitored for every BDI-II for each participant. If a participant at any time indicates an answer ≥ 1 on this item, we will have the participant complete a risk assessment using the Suicide Assessment Five-Step Evaluation and Triage (SAFE-T [87]) with Columbia Suicide Severity Rating Scale (C-SSRS [88]) Protocol, which describes the level of risk and subsequent response required by the research team.

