### Criteria for Early Discontinuation

Early discontinuation may occur due to one or more of the following reasons: (1) the participant’s decision not to continue the computerized training due to lack of time, interest, or motivation; (2) unavoidable circumstances (e.g., moving residence and unwilling or unable to return for in-person evaluations); (3) investigator decision to terminate; (4) death or prolonged hospitalization for medical reasons. We will not terminate participation for non-adherence. If non-adherence occurs, we will document the level of the participant’s adherence and still include the data in intent-to-treat analyses.

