#### Power.

Our preliminary study, with a sample of 46 participants, found significant within-subjects improvement across all outcomes and significant between-group differences in measures of EF and PS, with medium to large effect sizes for all findings [60]. Thus, with a recruitment goal of 90 participants in the current study, we expect to have significantly more power than our previous study. The power analyses for the current study were conducted using the pwr [98] and longpower [99,100] packages in R [101]. To power the proposed study at the 0.8 level (3 group RCT) to detect a medium between-group effect size (α = 0.05, two-tailed) with 20% attrition (a reasonable estimate based on our previous study [60] and consistent with dropout rates in psychotherapy RCTs [102]) would require a total sample of 195 or 65 per group. While this is obviously not feasible in a 3-year study (2.5 years actual recruitment, including database preparation, cleaning, and publication time at the end of the study) supported by a small grant mechanism, our proposed sample is twice that of our prior study. Also, in a previous study looking at CCN activation using the emotional go/no go task, significant activation was found in a number of different areas of the CCN with only 24 participants [103]. With a proposed sample size of 90, we are confident about detecting medium to large effect sizes across our proposed cognitive and neural activation variables of interest.

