* adapted from [60] with permission, copyright © Elsevier B.V.

**Table 4. T4:** Timeline of longitudinal assessments.

Measure	Screen	Baseline/Week 0	Week 4	Week 8	3-month follow-up
**ADIS-IV**	×				
**HDRS**	×	×	×	×	×
**BDI-II**	×	×	×	×	×
**SDS**	×	×	×	×	×
**WTAR**	×				
**Trail Making Test**		×	×	×	×
**Digit Span**		×	×	×	×
**Coding**		×	×	×	×
**Symbol Search**		×	×	×	×
**Letter Naming**		×	×	×	×
**Category Naming**		×	×	×	×
**Color-Word**		×	×	×	×
**CVLT-II**		×	×	×	×
**BVMT-R**		×	×	×	×
**Medication Check**	×	×	×	×	×

**Table 5. T5:** MRI and fMRI sequencing information.

Sequence	TR/TE/TI	Flip Angle	Resolution	FOV	Acquisition Time
**T1-MPRAGE**	2000/4.68/965	9	1 mm iso	256 × 312 × 192 mm	6′48″
**Resting state fMRI**	1500/30	73	2 mm iso	256 × 256 × 132 mm	4′
**Task-based fMRI**	1500/27	73	2 mm iso	256 × 256 × 132 mm	25′12″
**Resting state fMRI**	1500/30	73	2 mm iso	256 × 256 × 132 mm	4′

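### The BDI-II worsening rule ends study participation rather than training alone, so week-8 outcomes and the only follow-up MRI go uncollected because of a post-baseline outcome

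*Protocol article*

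**What the plan says.** All references are to the protocol article.

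- **Treatment Regimen** sets the rule: "if a participant shows a 20% increase from their baseline BDI-II score for two consecutive timepoints they will be discontinued from the study", with referral to mental health services. The object is the study; training is not mentioned.
- **Depressive symptoms criteria** makes the BDI-II an outcome that "will be used as a secondary measure of depressive symptoms" and has it "administered at all in-person visits and through an online survey format in weeks 2 and 6". The scores available to the rule up to the end of the trial phase are therefore those at weeks 0, 2, 4, 6 and 8.
- **CCT modules** gives waitlist participants no training until after 8 weeks, and says that they go through every assessment and imaging procedure.
- **Criteria for Early Discontinuation** opens "Early discontinuation may occur due to one or more of the following reasons" and lists four. The BDI-II rule is not named, although one item is termination by investigator decision. For non-adherent participants the section promises to "still include the data in intent-to-treat analyses". It gives no matching statement for participants who worsen.
- **Study Measures** places MRI at weeks 0 and 8 only.
- **Statistical Analysis and Sample Size** does not assume MCAR or MAR. It tests missingness by logistic regression on baseline predictors, and plans multiple imputation or maximum likelihood in place of deletion.

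**The concern.** A safety rule that ends data collection as well as treatment turns worsening into missing data. BDI-II measures the same construct as the primary mood outcome, HDRS, so participants are lost because of how they are doing on something close to the endpoint. The observed week-8 sample then under-represents those who got worse.

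Three things depend on this. Week-8 values of the primary outcomes HDRS, SDS and TMT-4 are lost for early triggers. The week-8 MRI, which the Aim 2 comparisons need, is lost with them. The correlation of clinical improvement with brain change would be estimated largely without the participants at the worsening end. With about 30 per arm, in a trial whose own power section says 195 would be needed for a medium effect, a handful of avoidable losses per arm matters.

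**Working it through.** **1. The plan's own example.** 22.98 × 1.2 = 27.58 and 23 × 1.2 = 27.6, so the first whole score that qualifies is 28. The 23-to-28 example in Treatment Regimen reproduces.

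**2. What each trigger costs.**

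| Consecutive timepoints | Rule is met at | Not collected afterwards |
|---|---|---|
| Weeks 2 and 4 | week 4 | week 8 (HDRS, SDS, TMT-4, MRI) and 3-month visit |
| Weeks 4 and 6 | week 6 | week 8 (HDRS, SDS, TMT-4, MRI) and 3-month visit |
| Weeks 6 and 8 | week 8 | mainly the 3-month visit |

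**3. What discontinuation can mean.** In the two training arms it might be read as stopping training. In the waitlist arm there is no training before week 8, so up to then the rule can only stop assessment. That does not sit with the CCT modules statement that waitlist participants complete all assessment and imaging.

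**4. How often it would fire.**

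Inputs from the protocol: baseline mean 22.98 and SD 11.58 (preliminary study, Treatment Regimen); BDI-II at weeks 0, 2, 4, 6, 8; 90 participants in three arms, taken as 30 each.

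Assumptions not in the protocol: measurement-error SD σ of 3–5; SD τ of individual 8-week change of 4–8; mean 8-week change m of 0 or −6; normal distributions.

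Model: Y(t) = b + s·t/8 + e(t), rounded and held within 0–63, with b ~ N(22.98, 11.58² − σ²), s ~ N(m, τ²), e(t) ~ N(0, σ²). The trigger by week 6 is Y ≥ 1.2·Y(0) at weeks 2 and 4, or at weeks 4 and 6.

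| σ | τ | m = 0 | m = −6 |
|---|---|---|---|
| 3 | 4 | 14% | 5% |
| 3 | 5 | 15% | 6% |
| 3 | 8 | 19% | 9% |
| 4 | 5 | 19% | 9% |
| 4 | 8 | 21% | 11% |
| 5 | 5 | 22% | 12% |
| 5 | 8 | 24% | 14% |

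Per arm of 30: 30 × 0.14 = 4.2 to 30 × 0.24 = 7.2 with no mean change, and 30 × 0.05 = 1.5 to 30 × 0.14 = 4.2 at −6. Under matched assumptions the gap is about 9–11 percentage points, or 3 participants. Counting weeks 6 and 8 as well raises the no-change share by a further 5–7 points (for example 21.4% to 28.0% at σ = 4, τ = 8). Those triggers do not cost the week-8 visit.

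**5. What it does to the observed data.** At σ = 4, τ = 8, the mean week-8 BDI-II change among those still observed is about −2.5 where the full-arm value is 0.1, and about −7.0 where it is −5.5. Both arms look better than they are, the non-improving arm more so.

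**6. Bias in the HDRS comparison.** HDRS was assumed to track BDI-II at half scale, with a true 8-week difference of −3.0. Three large simulated trials (4,000 per arm) gave −2.76 to −2.81 from observed cases, and −2.88 to −2.94 from a maximum-likelihood random-slope model (standard errors 0.10–0.12). Any bias runs toward no difference and is small under likelihood estimation.

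**7. MRI.** With scans at weeks 0 and 8 only, the Aim 2 t-tests and the regressed-change model need the week-8 scan. No intermediate scan carries information about the missing one. The size of any bias cannot be computed, because the protocol gives no relation between BDI-II change and the imaging measures.

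**8. The missingness check.** Regressing missingness on baseline variables cannot show a mechanism that acts on BDI-II at weeks 2, 4 and 6.

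**The case against.** The strongest reply is that the analysis plan already copes. Deletion methods are rejected, maximum likelihood or multiple imputation is planned, and the trigger depends on recorded BDI-II scores that an imputation model can use. For HDRS this largely stands, as step 6 shows. It does not supply the missing MRI, and the protocol does not say that post-baseline BDI-II will enter the models.

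A second reply is that an article leaves post-discontinuation follow-up to the full protocol. That would answer silence. Here the text states that participation in the study ends, and says elsewhere that waitlist participants complete everything.

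Several stronger readings are tempting, and the document does not support them:

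- *That intent-to-treat is broken.* Missing later visits does not change analysis as randomised, and nothing says that collected data are discarded. The quoted intent-to-treat sentence concerns non-adherence only.
- *That the list of discontinuation reasons contradicts the rule.* It omits the rule, but investigator decision can absorb it. This is a gap.
- *That Table 4 conflicts with the text because it shows no week-2 or week-6 BDI-II.* Its columns are the clinic visits. It does not override two explicit statements about online administration.
- *That the 20% attrition figure leaves the rule out.* That figure is based on the previous study, and whether that study had such a rule is not stated. It also feeds the 195 that will not be recruited.
- *That a 2-point rise suffices one SD below the mean.* 22.98 − 11.58 = 11.4; at a baseline of 11, 11 × 1.2 = 13.2, so 14 is needed. That is a 3-point rise, at two consecutive timepoints. The threshold is described as a clinical decision and is not disputed here.

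**Conclusion.** The point holds in a limited form. As written, the rule stops later data collection because of a post-baseline outcome, can remove the week-8 primary measurements and the only follow-up scan, and is invisible to the planned missingness check. Data already collected are not lost.

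The likely size is 4–7 of 30 in an arm with no mean change and 2–4 of 30 in an arm improving by 6 points. This rests on the assumed error and change SDs, and no trial data on worsening are available. A reader might infer that the waitlist arm will certainly lose more. The protocol gives no worsening rate by arm, and the imbalance follows only if its own hypothesis of less improvement on waitlist is true. HDRS bias is probably small under the planned methods. The main exposure is Aim 2 and the loss of precision. The change is worth making, but the trial does not fail without it.

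**What to change.** 1. Reconcile Treatment Regimen, CCT modules and Criteria for Early Discontinuation on whether the rule ends training or all assessment, and name the rule among the discontinuation reasons. The threshold and the safety action are for the clinical lead.
2. Record stopping training separately from leaving assessment. Keep participants who consent in whatever remains of the scheduled week-4, week-8 (including MRI) and 3-month assessments. Analyse them as randomised, with referral recorded.
3. Add post-baseline BDI-II to the missingness models and to the imputation model.
4. Report rule-driven discontinuations by arm and by the timepoint at which they occurred.

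If every such participant consented, the week-8 loss due to this rule would be zero. The cost is a short amendment and revised consent wording; the visits and scans are already scheduled. The downside is that some week-8 data will come from participants in referred care, which is why referral should be recorded.
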